## Abstract

**Background:**

The likelihood of an adolescent taking up smoking may be influenced by his or her society, school and family. Thus, changes in the immediate environment may alter a young person’s perception of smoking.

**Methods/Design:**

The proposed multi-center, cluster-randomized controlled trial will be stratified by the baseline prevalence of smoking in schools. Municipalities with fewer than 100,000 inhabitants will be randomly assigned to a control or intervention group. One secondary school will be randomly selected from each municipality. These schools will be randomized to two groups: the students of one will receive any existing educational course regarding smoking, while those of the other school will receive a four-year, class-based curriculum intervention (22 classroom lessons) aimed at reinforcing a smoke-free school policy and encouraging smoking cessation in parents, pupils, and teachers. The intervention will also include annual meetings with parents and efforts to empower adolescents to change the smoking-related attitudes and behaviors in their homes, classrooms and communities.

We will enroll children aged 12-13 years as they enter secondary school during two consecutive school years (to obtain sufficient enrolled subjects). We will follow them for five years, until two years after they leave secondary school. All external evaluators and analysts will be blinded to school allocation.

The aim of this study is to analyze the effectiveness of a complex intervention in reducing the prevalence of smoking in the third year of compulsory secondary education (ESO) and two years after secondary school, when the participants are 14-15 and 17-18 years old, respectively.

**Discussion:**

Most interventions aimed at preventing smoking among adolescents yield little to no positive long-term effects. This clinical trial will analyze the effectiveness of a complex intervention aimed at reducing the incidence and prevalence of smoking in this vulnerable age group.

**Trial registration:**

Current Controlled Trials: NCT01602796.

## Background

Tobacco use is a known risk factor for many chronic illnesses; it is the main cause of avoidable mortality in Europe, and it is responsible for 4.2 million deaths per year worldwide [1,2]. The prevalence of tobacco use among adolescents in the European Union is high, with approximately 15% of 14- and 15-year-olds smoking, although this percentage varies from 7% to 23% among countries [3]. Some countries have reported a change in the pattern of initial consumption in recent years, with more girls beginning to smoke, especially among younger age groups [4]. Within any given country, a high variability in smoking behavior is seen across schools [5-7].

The various factors associated with taking up smoking can be grouped into three categories, individual, social and cultural factors [8]. Individual factors are intrinsically linked to a given person and include the individual’s age and certain cognitive, emotional and biological aspects. The factors associated with the immediate social context (i.e., the environment closest to the adolescent) include the smoking-related attitudes and behaviors of family members and friends. The factors associated with the socio-cultural environment (i.e., the wider social context) include the smoking policy of the adolescent’s school.

Around 70% of current smokers began smoking before the age of 18 years, and those who do not begin to smoke by this age are highly unlikely to become smokers as adults [9]. Preventing young people from starting to smoke and helping young smokers break the habit are currently the most effective means to reduce the number of deaths attributable to smoking in the medium and long terms. To this end, various European countries have introduced programs designed to prevent tobacco use. Such programs should be based on scientific evidence and seek to reach children before they commence smoking.

A review of the effectiveness of distinct school- and/or community-based interventions to prevent smoking [10] indicates that multi-sector interventions (i.e. those involving the classroom, school, extracurricular activities, family, and community) yield more promising results than single-sector interventions. Furthermore, the evidence suggests that school-based preventive programs are not effective on their own; instead, interventions should be community-based, and should have impacts in the classroom, the school environment, and the community [11].

We propose to carry out a cluster-randomised controlled clinical trial to analyse the effectiveness of a multifactorial intervention addressed to adolescents and, in particular, their environment (educational centre, teachers and parents), as we believe that altering the adolescents’ immediate environment could have a considerable effect on reducing tobacco use among the young.

Cluster randomization is required because the interventions will be implemented at the school level.

## Methods

### Design and environment

This prospective multi-center cluster-randomized controlled trial will involve schools and communities stratified by school-level tobacco consumption at baseline. The clusters will consist of municipalities in the Balearic Islands. Control schools will continue to implement any smoking-prevention activities that are already in place when the study begins.

### Inclusion criteria

The Balearic island is organized into four insular councils (Majorca, Minorca, Ibiza and Formentera) and those in municipalities. There is 53 municipalities in Majorca and 8 in Minorca, between 300 to 350,000 inhabitants. All Balearic Island municipalities in Majorca and Minorca having fewer than 100,000 inhabitants and at least one public compulsory secondary-educational institution will be included. In municipalities containing more than one secondary school, the secondary school to be included will be determined through a randomization process. If the selected school declines to participate, another school from the same municipality will be invited to take part.

### Study population

The populations of the included municipalities vary from 11,000 and 30,000 inhabitants. The main economic activities of these communities are tourism and farming.

The study participants will consist of all 12-13 year-old students, who enrolled in the first grade of compulsory secondary education (ESO) over two consecutive academic periods (i.e., 2011-12 and 2012-13). The intervention will take place over the four years during which these adolescents are enrolled in ESO. Written informed consent will be obtained from all students and from at least one parent/guardian per student, according to the declaration of Helsinki.

### Pilot study

A pilot program is currently underway in a single public secondary education center to test the proposed intervention, the materials, and the data-collection networks. Following the four-year intervention and follow-up, data will be gathered and evaluated. We plan to implement the full study at the two-year mark of the pilot program.

### Recruitment

Headmasters at the selected schools will be contacted by a research team member, who will provide details about the study and invite the school to participate.

### Random assignment

Once informed consent and the commitment to participate have been obtained from the students/parents and the school, respectively, a baseline survey will be performed to determine the prevalence of smoking. Thereafter, the participating schools will be subjected to stratified randomization according to the baseline prevalence of tobacco use at each school by the “random” module, and the option separate strata of PEPI (version 4.0, Sagebrush Press).

### Measurements

Table 1 summarizes the study measurements, variables and schedule. The baseline questionnaire will gather data on a given student’s sociodemographic characteristics, environment and tobacco use, and the attitudes of his/her parents and teachers towards smoking. The smoking question was adapted from a previously validated questionnaire for adolescents [12]. Information on tobacco use will be collected through the following question: *Which of the following statements best describes you? (A) I have never tried to smoke; (B) I have tried cigarettes a few times, but I do not smoke now; (C) I currently smoke less than one cigarette per month; (D) I currently smoke at least one cigarette per month, but less than one cigarette per week; (E) I currently smoke at least one cigarette per week; (F) I smoke every day; (G) I used to smoke regularly in the past, but I do not smoke now.*

**Table 1 T1:** Measures, questionnaires and timeline

**Instrument**	**Assessment area**	**Timing of assessment**
Pre-test questionnaire	Baseline prevalence of smoking	Before randomization
Baseline data form	Student smoking behaviors	At baseline
Teacher baseline data form	Teacher smoking behaviors and attitudes towards smoking and prevention	At baseline
Parent baseline data form	Parent smoking behaviors and attitudes towards smoking	At baseline
Smoking prevalence form	Prevalence of smoking among adolescents	After the fourth year of ESO and two years after graduation

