The components of the social-influences model that will integrated into this curriculum include teaching students to identify the social influences that encourage people to start smoking (e.g., tobacco company advertising campaigns, peer pressure), providing information about the harmful effects of smoking, and nurturing refusal skills. The curriculum will include anti-advertising workshops that are designed to sensitize participants to the power of advertising. The intervention will also seek to: debunk false beliefs about tobacco; encourage positive means for coping with emotion, stress and peer pressure; and help students develop interpersonal relationship skills, self-esteem, strategies for accepting rules and limits, critical thinking skills, problem-solving skills, and the ability to recognize risky situations.

The classroom sessions will be given by trained teachers in the intervention components, smoking prevention and Health. It will consist of seven lessons in the first year (ages 12-13), six lessons in the second year (ages 13-14), five lessons in the third year (ages 14-15) and four lessons in the fourth year (ages 15-16) of ESO. All lessons will be age-appropriate and relevant to the students’ curricula. All lessons will include material that students will work on together with their parents.

#### **
*Families*
**

The parents of our participants will meet with the personnel of the study, at least once per year at the beginning of each academic to receive information about the intervention and learn how they can help keep their children from smoking. These meetings will focus on encouraging parents to: have an appropriate attitude towards drug use; recognize situations that constitute a risk for adolescents; establish rules and limits; be sensitive to the role that family plays in tobacco use; and participate in the smoke-free home initiative. At least once per year, a workshop on smoking cessation will be held for the participating families of each municipality.

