### Strategies to ensure implementation of the intervention and avoid loss to follow-up

For the project to be successful, we will need to maintain our collaborations with the schools for at least four years. Therefore, all activities associated with the project must conform to the needs and interests of each school. Specific activities will be designed to promote continuity, including visits by the research team and periodic mailings to each school informing them of the progress of the study and recognizing their crucial role. The importance of the control group in the study will also be emphasized.

The final follow-up evaluation will occur six years after inclusion, when the participants will have left the participating school. At least three telephone contact numbers and the addresses of parents and tutors will be obtained early in the study. If a student is not easily located for the final evaluation, additional efforts will be made to contact them by telephone and letter. Efforts will be made to minimize the rate of loss to follow-up to reduce any possible bias resulting from loss to follow-up and to adequately assess the impact of the intervention.

#### **
*Outcome assessments*
**

The measures, variables, and timeline are summarized in Table 1. The baseline prevalence of smoking in each school will be assessed by an external evaluator who will be blinded to the group (intervention or control) to which the school has been allocated. All outcome assessors and data analysts will also be blinded to school allocation. To evaluate the effectiveness of blinding, these individuals will be asked to choose the arm to which they believe each school was assigned (possible answers: intervention, control, or unknown). Individuals who respond “intervention” or “control group” will be asked to indicate what led to the formation of that belief. The primary outcome measure will be the prevalence of smoking at years three and six from enrollment. This will be assessed by self reports of tobacco consumption, where smokers are defined as those who consume more than one cigarette per week.

#### **
*Statistical analysis*
**

##### 

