**Sample size** A recent study on smoking in adolescents aged 14-15 years (third year of ESO) found that the prevalence of regular tobacco use in the Balearic Islands was 14% [13]. Using this as the prevalence for our control group and presuming that our intervention will reduce the prevalence of tobacco consumption in the intervention group by at least 40%, the use of 1,002 students per group will yield a statistical power > 80% for our between-group comparisons, assuming a bilateral α error of 5% and a 10% loss of participants to follow-up. The cluster size will be approximately 100 adolescents per municipality; we expect a 0.02 intra-class correlation coefficient [14], yielding a 2.98 cluster design effect. The design effect was calculated using the formula: Deff = 1 + (m – 1) * ICC; where “Deff” corresponds to the design effect, “m” is the cluster size and “ICC” is the intraclass correlation coefficient. The target sample size for each group was calculated to be 1,113 students, or 2,226 students in total. To achieve this sample size, students in the first year of ESO (aged 12-13 years) will be recruited over two consecutive years at 22 schools in the Balearic Islands.

##### 

**Analytic strategy** We will test for significant differences in baseline characteristics between the control and intervention groups. We will perform a descriptive and cluster analysis with continuous variables summarized using means and standard deviations for normal distributions, and by medians and 25^th^ and 75^th^ percentiles for non-normal distributions. All data analyses will involve intention-to-treat populations (i.e., all randomized patients, regardless of participation in any treatment session). This approach will reduce the bias that may occur when participants that fail to receive the assigned treatments are excluded from the analysis. All tests will be two-sided, and α-values of 0.05 will be considered statistically significant.

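### The timing of the first primary endpoint is contradictory: third year of ESO in the aim, outcome and sample size, after the fourth year in Table 1, and 12 months in the analysis section

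*Protocol article*

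**What the plan says.** Three places in the protocol article put the first endpoint in the third year.

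- Abstract, Methods/Design: the aim is "reducing the prevalence of smoking in the third year of compulsory secondary education (ESO) and two years after secondary school", with ages 14-15 and 17-18 attached to the two points.
- Outcome assessments: "The primary outcome measure will be the prevalence of smoking at years three and six from enrollment".
- Statistical analysis, Sample size: the control rate comes from the third year. "A recent study on smoking in adolescents aged 14-15 years (third year of ESO) found" a regular-use prevalence of 14%.

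Two places say otherwise.

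- Measurements, Table 1: the smoking prevalence form is due "After the fourth year of ESO and two years after graduation". Every other row is before randomization or at baseline.
- Statistical analysis, Analytic strategy: the between-group comparison of prevalence is set at 12 months.

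Table 1 is not a side note. Outcome assessments itself says "The measures, variables, and timeline are summarized in Table 1".

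Follow-up length is also given in two ways. The Abstract has "We will follow them for five years, until two years after they leave secondary school", while the section on avoiding loss to follow-up has "The final follow-up evaluation will occur six years after inclusion".

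**The concern.** The outcome text defines one time point and then refers the reader to a schedule that holds a different one. The third and fourth years of ESO are separate in this document, each with its own age band and its own lessons. The analysis section adds a third time point for which no form is scheduled.

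At stake is when the primary endpoint is observed and tested. A third-year survey of a given school cohort cannot be recovered once that year has passed. A wave after the fourth year would measure older pupils who had received more of the intervention, so the planning prevalence would no longer describe the endpoint analysed. With three candidate times in print, the choice of the time that counts is also open to being made after data are seen.

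**Working it through.** No recalculation of the sample size is needed. The check sets the stated times side by side on one scale.

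**Ages and lessons.** Intervention, Classroom sessions gives seven lessons in the first year (age 12-13), six in the second (13-14), then "five lessons in the third year (ages 14-15) and four lessons in the fourth year (ages 15-16) of ESO". The total is 7 + 6 + 5 + 4 = 22, which reproduces the stated 22.

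| Place in the protocol article | First follow-up time | Age | Lessons delivered by then |
|---|---|---|---|
| Abstract, aim | third year of ESO | 14-15 | 13 to 18 of 22 |
| Outcome assessments | year three from enrollment | not stated | at most 18, if read as the third year |
| Sample size | third year of ESO | 14-15 | not applicable (source of the 14%) |
| Measurements, Table 1 | after the fourth year of ESO | 15-16 | 22 of 22 |
| Analytic strategy | 12 months | not stated | about 7, if counted from entry |

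The lesson counts are 7 + 6 = 13 at the start of the third year, 13 + 5 = 18 at its end, and 18 + 4 = 22 after the fourth. The aim does not say when in the third year the survey falls, hence a range.

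**Calendar.** Study population gives entry in 2011-12 and 2012-13. The third year of ESO is then 2013-14 and 2014-15 for the two cohorts, and the fourth year is 2014-15 and 2015-16. Table 1's first wave follows the end of the fourth year, so it falls at least one school year after the end of the third.

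**Can the two be reconciled by counting differently?** In completed school years, the end of the fourth year is year four, not three. By difference in age bands, 15-16 is three years above 12-13, so year three could be read as the fourth year of ESO. That reading fails twice. The same count puts the final wave (17-18) at year five, while the outcome says six. The aim and the sample size also name the third year of ESO and age 14-15 outright.

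**The 12-month comparison.** Counted from entry, it falls around the end of the first year or the start of the second. Table 1 has no smoking form there, and neither primary time point is near it.

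**Does the planning prevalence carry over?** The 14% is a Balearic figure for age 14-15. The Discussion reports that regular smoking in the European Union rises from 5% at 12 to 21% at 16. That supports a strong age gradient, but it gives no Balearic rate at 15-16. So the 14% cannot be assumed for Table 1's wave, and the documents do not say what should replace it.

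**Follow-up length.** Four years of ESO plus two years is 4 + 2 = 6. By age band, entry at 12-13 and final evaluation at 17-18 differ by 5. The two figures can describe the same wave under different counting conventions.

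**The case against.** The strongest reply is that three statements agree on year three and one cell of a summary table does not, so that cell is probably a slip of fourth for third. The Limitations section leans the same way: the pilot's first evaluation survey was of 14-year-olds. This is plausible, and it stands against a flat claim that the year-three endpoint will not be collected. A reader might infer that from Table 1, but the documents support only the conditional: it would be missed if Table 1 were followed as written. The reply does not remove the contradiction, because nothing in the article says which version governs and the outcome section defers to the table.

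A reader might also infer a loss of power. The documents do not support that. They give no control rate for the region at 15-16, and a higher rate with the same relative reduction would raise power rather than lower it. Whether the stated sample size is adequate is a separate question.

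Finally, a reader might take five against six years as two different measurement dates. The Abstract's own ages span five years and its wording ends two years after school, so one wave counted in two ways is a fair reading. Only a wording point remains.

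**Conclusion.** The contradiction stands and needs correcting before the schedule is used. The aim, the primary outcome and the planning prevalence sit in the third year of ESO. The cited timeline has no third-year measurement, and the analysis section tests at a time that matches no scheduled follow-up wave.

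The gap between the outcome and Table 1 is one school year of age (14-15 against 15-16) and at least 22 - 18 = 4 lessons. It is up to 22 - 13 = 9 lessons if the third-year survey came at the start of that year. This assumes lessons are delivered in the years listed and that year three means the third year of ESO, as the aim says. The conclusion does not depend on any power calculation. The conflict between the documented times is certain. Whether the endpoint would in practice be missed is not, and depends on which text the survey teams follow.

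**What to change.** In Measurements, Table 1, set the smoking prevalence form to the third year of ESO and two years after leaving ESO. In the Analytic strategy, replace the 12-month comparison with the same two time points. If the survey is to fall at a fixed moment within the third year, state it; the article does not.

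If the fourth-year wave is the one intended, leave Table 1's first time and instead change the aim, the outcome definition and the planning prevalence to age 15-16. That needs a control rate for that age, which the article does not give, and the sample size would have to be worked again. The 12-month comparison must be changed in this case too.

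As a secondary wording change, give one follow-up length in the Abstract and in the section on loss to follow-up, state how years are counted, and make the ages agree with it.

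Cost: if Table 1's entry is a slip, this is wording only. If it reflects the real field plan, the first survey moves by about a school year in the 22 schools, with no wave added. The real price of the first option is that it gives up the measurement at completion of the four-year intervention. Keeping that as well would mean an extra survey round.

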### Intervention

ITACA (“multifactorial intervention to reduce the prevalence of smoking in the adolescent population: a cluster-randomized trial”) is a cognitive-behavioral intervention based on the social-influences model. It is designed to prevent adolescents from starting to smoke and to empower them to change the smoking-related attitudes and behaviors within their immediate environments, including their homes, classrooms and communities (e.g., neighborhoods, town squares and/or villages). This intervention will be integrated into the schools’ curricular activities. The main components of this intervention and the activities to be performed are summarized in Table 2.

**Table 2 T2:** Intervention components

**Component of the intervention**	**First year (age 12-13 years)**	**Second year (age 13-14 years)**	**Third year (age 14-15 years)**	**Fourth year (age 15-16 years)**
**School-based interventions**	Seven lessons: two on information about the harmful effects of smoking; four on refusal skills (self-esteem, interpersonal relationship skills, problem-solving skills, ability to recognize risky situations, and strategies for accepting rules and limits); and one on identifying social influences that encourage people to start smoking, and smoking cessation	Six lessons: three about the harmful effects of smoking; one on refusal skills (interpersonal relationship skills and critical thinking); two on identifying social influences that encourage people to start smoking (tobacco company advertising campaigns, debunking false beliefs about tobacco), and smoking cessation	Five lessons: three on refusal skills (strategies for accepting rules and limits, problem-solving skills, group pressure, self-esteem and coping with emotion and stress); two on identifying social influences (debunking false beliefs about tobacco, and anti-advertising workshops designed to sensitize people to the power of advertising), and smoking cessation	Four lessons: one on the harmful effects of smoking; one on refusal skills (critical thinking and problem-solving skills); two on identifying social influences that encourage people to start smoking (tobacco company advertising campaigns, debunking false beliefs about tobacco), and smoking cessation
**Parental interventions**	Two work meetings focused on parental attitudes towards drug consumption and helping parents recognize risky situations, establish rules and limits, understand the family’s role in tobacco use and the smoke-free home initiative, and implement smoking cessation	Two work meetings focused on parental attitudes towards drug consumption and helping parents recognize risky situations, establish rules and limits, understand the family’s role in tobacco use and the smoke-free home initiative, and implement smoking cessation	Two work meetings focused on parental attitudes towards drug consumption and helping parents recognize risky situations, establish rules and limits, understand the family’s role in tobacco use and the smoke-free home initiative, and implement smoking cessation	Two work meetings focused on parental attitudes towards drug consumption and helping parents recognize risky situations, establish rules and limits, understand the family’s role in tobacco use and the smoke-free home initiative, and implement smoking cessation
	Collaborate with the student on homework regarding parental tobacco habits and attitudes, social norms and passive smoking	Collaborate with the student on homework regarding parental tobacco habits and attitudes, social norms and passive smoking	Collaborate with the student on homework regarding parental tobacco habits and attitudes, social norms and passive smoking	Collaborate with the student on homework regarding parental tobacco habits and attitudes, social norms and passive smoking
**Teacher interventions**	Teacher training on: competences related to smoking prevention in adolescents; managing conflict situations; attitudes towards preventive activities; information on the prevalence of smokers in the educational center; and smoking cessation	Smoking cessation.	Smoking cessation	Smoking cessation
**Smoke-free policy reinforcement**	The schools will be invited to adopt a smoke-free environment, implement the school’s own rules, and establish rule-compliance indicators			

#### **
*Classroom sessions*
**

The four-year curricular component will consist of 22 lessons of approximately 50 minutes each, including eight lessons that will be presented as part of the environmental sciences curriculum, six as part of the social sciences curriculum, two as part of the physical education curriculum, one in the mathematics curriculum, and five that will be presented as student tutorials.

The components of the social-influences model that will integrated into this curriculum include teaching students to identify the social influences that encourage people to start smoking (e.g., tobacco company advertising campaigns, peer pressure), providing information about the harmful effects of smoking, and nurturing refusal skills. The curriculum will include anti-advertising workshops that are designed to sensitize participants to the power of advertising. The intervention will also seek to: debunk false beliefs about tobacco; encourage positive means for coping with emotion, stress and peer pressure; and help students develop interpersonal relationship skills, self-esteem, strategies for accepting rules and limits, critical thinking skills, problem-solving skills, and the ability to recognize risky situations.

The classroom sessions will be given by trained teachers in the intervention components, smoking prevention and Health. It will consist of seven lessons in the first year (ages 12-13), six lessons in the second year (ages 13-14), five lessons in the third year (ages 14-15) and four lessons in the fourth year (ages 15-16) of ESO. All lessons will be age-appropriate and relevant to the students’ curricula. All lessons will include material that students will work on together with their parents.

#### **
*Families*
**

The parents of our participants will meet with the personnel of the study, at least once per year at the beginning of each academic to receive information about the intervention and learn how they can help keep their children from smoking. These meetings will focus on encouraging parents to: have an appropriate attitude towards drug use; recognize situations that constitute a risk for adolescents; establish rules and limits; be sensitive to the role that family plays in tobacco use; and participate in the smoke-free home initiative. At least once per year, a workshop on smoking cessation will be held for the participating families of each municipality.

One novel aspect of the intervention is that 20% of the curricular sessions will ask the student to involve their families in home-based tasks related to smoking prevention. Furthermore, a minimum of three leaflets will be provided each year regarding smoking in adolescents. The leaflets will contain answers to questions frequently asked by families, along with support material from the curricular sessions that parents and students can work on together. Parents will also receive information on make your home a smoke-free. Finally, parents will have access to a webpage that offers information on the school intervention, tips on how families can help prevent children from smoking, and advice on smoking cessation in adolescents.

#### **
*Teachers and the school’*
**

Prior to the start of the intervention, the teachers of the enrolled schools will participate in training course. During this course, the needs of the teaching staff regarding smoking prevention and health themes will be identified. This course has been recognized by local government boards of education. Each school will designate a coordinator to carry out the intervention.

Classroom lessons will be subject to approval according to the school’s internal rules, and a communication system involving the coordinator, the teachers and the project researchers will be established. Annual meetings will be held with the school management team to reach agreements on the application of current legislation and the organizational structure of each smoke-free school. Teachers will participate in an initial on-line 20-hour training workshop. They will be instructed on skills related to smoking prevention in adolescents and management of conflict situations. This workshop will also address the teachers’ attitudes towards drug use and instruct them on preventive activities that will promote health.

The participating schools will be invited to adopt a smoke-free environment policy. The teachers at each school will hold a meeting to establish the school’s rules with respect to tobacco use by pupils and teachers. Each school will: implement its own rules; evaluate compliance; inform all teachers, students and parents of the changes being made to the rules; and establish a means to assess and record rule-compliance indicators, including incidents involving students and others smoking in the school.

The protocol for implementing the basic curriculum and the supplementary components of the intervention have been standardized in an effort to homogenize the intervention. The supplementary components include: the timing and contents of the lessons; agendas for the teachers’ meetings; the contents of the initial teacher-training workshop; the contents of the parental meetings; and the establishment of a professional advice network for parents and teachers who decide to quit smoking during the study.

